## Abstract

Physiotherapy education in Europe must incorporate self-study units in the curriculum due to the bologna reform. Studies investigating the impact of guided self-study (G-SS) on knowledge and skills in pre-clinical Swiss physiotherapy students are scarce. This study protocol describes a prospective randomized feasibility education study that will primarily examine the feasibility of establishing G-SS using retired physiotherapists as tutors in undergraduate physiotherapy students at the Bern University of Applied Sciences, School of Health Professions. Secondary objective will be to evaluate the effectiveness of six G-SS cycles with retired physiotherapists as tutors on knowledge and skills of pre-clinical undergraduate physiotherapy students. Students of the physiotherapy degree course will be allocated into a G-SS group or control group (CG). G-SS consists of an 8-day cycle. Feasibility outcome are the fidelity of implementation that include exposure dosage and students’ responsiveness, and the degree of acceptability. Success criteria of feasibility are (1) exposure dosage calculated as the number of 90-min presentations that are conducted, and the content of cases and competences and (2) students’ responsiveness, with at least a 83% willingness to participate. Acceptability of intervention from the undergraduate students’ perspective will be evaluated by a questionnaire with open, semi-structured questions (post intervention). This study will provide new information regarding the feasibility of embedding G-SS in the curriculum and about the students’ responsiveness and their acceptability for G-SS.

Study protocol version 1

**Trial registration:** German Register of Clinical Studies (DKRS: DRKS00015518).

## Introduction

As a part of the Bologna process, higher education institutions across the European Union were required to write their study programs and modules in terms of learning outcomes to enable the transition to the” student-centered approach (SCA)” of the European Credit Transfer System (ECTS) (1). Learning outcomes define what a student is expected to know and/or is able to demonstrate after successful completion of the degree program (1). Learning outcomes present a shift from traditional learning models that focus on inputs such as content and teaching hours towards SCA that focuses on outputs in terms of student competences (1). ECTS was introduced to provide a better representation of the students’ workload for learning and to achieve the learning outcome, respectively. The workload included work in- and outside the classroom e.g., frontal teaching, exams, self-study (SS) and for example preparation and follow-up of courses and exams expressed students time investment, whereby one credit corresponds to a workload of 25–30 h (2).

The first bachelor’s degree course (BSc) in physiotherapy at the Bern University of Applied Sciences, School of Health Professions (BFH-SHP) was launched in September 2006, with a total amount of 180 ECTS. The BFH-SHP guidelines recommend a workload ratio of 40% contact study (e.g., frontal teaching, seminars, workshops) to 60% of time for self-study (3) during a module. A module can be described as a self-contained, structured thematic unit, the scope of which is defined in learning outcomes with specified assessment criteria and ECTS credits (4).

Self-reliant learning is one of the most important components that needs to be developed while studying (4). This is described in the fifth category of the Dublin Descriptors – “learning skills” – and is to be promoted during contact studies as well as during self-study. During contact study, students are encouraged to engage in dialogue, reflection and self-critical action through adequate forms of knowledge transfer (e.g., frontal teaching, seminars, and workshops) and elaboration and the assignments. The lecturers offer students the opportunity to work on tasks independently and to provide direct feedback (4).

Landwehr and Mueller (5) and Rogan (6) described three types of self-study. The first type is free self-study (F-SS). In F-SS students set their goals, specific topics and content and develop them voluntarily according to their own interests. The second type is called individual self-study (I-SS). In I-SS self-study the students work on in greater depth, without learning outcome and work orders from lectures. The third form is guided self-study (G-SS), in which students develop knowledge, skills and competences primarily on their own but with some support of lecturers who will behave more as “coaches”. During the processing of tasks, students are supported by the lecturers. Lecturers give feedback about the process and results. The lecturers define suitable tasks that enable the students to achieve the competences that are to be developed during guided self-study. These tasks are independent respectively not linked to the learning outcomes of the contact study.

F-SS and G-SS were scheduled in the BSc physiotherapy curriculum. Students may use the F-SS to prepare for lectures (contact study) or for exam preparation or to write an essay or work on a group project or may decide themselves on which module content they want to work and learn (3). During G-SS physiotherapy students themselves may decide what they want to work on and learn under the supervision of a university lecturer (3). The university lecturer is available during this time for questions or to demonstrate or adjust practical examination and treatment techniques.

A critical stage for self-study is the initial study phase: in comparison to school, students at undergraduate level are now expected to be more independent, and usually learn more and faster (7). Harvey et al. (8) postulated that the experience of being a first-year student who is “one of all,” and was not considered as an individual, is one of the main issues of students learning. Yorke (9) suggested that the focus of the first year of study should be on addressing individual student needs, rather than viewing first-year students as a potentially problematic group of students. To support students in this phase, a well-designed concept of G-SS is needed.

Schmidt et al. (10) stated that the curriculum content plays a role in how many students graduate and how fast they graduate. In their study, they collected from 14,000 medical students study duration and graduation rate. Medical students were enrolled in eight Dutch Universities between 1989 and 1998. They were able to demonstrate that the more time available for self-study, the higher the number of students who graduated 5–8 years later. The number of classroom lessons was negatively related to graduation rate. This means, the more classroom lessons were planed and were given, the lower the graduation rate. Furthermore, a higher degree of self-study time was associated with a shorter duration of study. Lessons had a negative impact on study duration. The number of tutorial sessions and internships were not related to the outcome variables, but both were moderately negatively related to the number of classes: the more classes in a curriculum, the fewer tutorials and internships. The literature describes that a curriculum that is prioritizing small group instruction rather than classroom teaching as the primary method of instruction generally, have higher graduation rates than other types of curricula (11, 12). G-SS can focus on small groups or individual work.

### Guided self-study in higher education

Landwehr and Müller (5) postulated a five-phase concept for G-SS, in which university lecturers may guide students. Phase 1: Initiation - students will be assigned to groups and will receive a clinical case which is aligned with the curriculum content; Phase 2: Realization - students prepare the case in small groups; Phase 3: Presentation - students present their results to the lecturers and peers in a moderated plenum session; Phase 4: Evaluation – students perform a self-evaluation. Phase 5: University lecturer gives feedback to the students.

Rogan (6) described a theoretical construct of how a G-SS should be designed to change knowledge and skills among undergraduate physiotherapy students. Based on this theoretical construct, Rogan et al. (13, 14) have conducted two G-SS feasibility studies with university lecturers as tutors.

Both G-SS feasibility studies evaluated the fidelity of implementation as exposure (e.g., time duration of phases 3 to 5), students responsiveness and program differentiation. In addition, changes in knowledge and skills were assessed after a total of six G-SS cycles in first-semester (13) and after three G-SS cycles in the third semester (14) respectively. Both studies demonstrated that the G-SS must be scheduled in periods with a low workload, to increase the students’ responsiveness to G-SS. Furthermore, it could be illustrated that students who performed all six G-SS cycles (first semester) and all three G-SS cycles (third semester) showed a higher likelihood to pass written and practical exams as compared to students in the control group (F-SS: 1. Semester; *n* = 4 out of 25, and 3. Semester; *n* = 2 out of 26). Furthermore, six G-SS cycles resulted in a significant chance in knowledge in the G-SS group compared to the control group. No differences were determined after three G-SS sessions.

This form of teaching seems to have the potential that examination and treatment techniques can be learned by students from all health professions and medicine in G-SS. However, resources of lecturers are not endless. For this reason, retired physiotherapists will be used as tutors in the upcoming study. On the one hand, they have many years of experience and on the other hand, several students can be supervised in the same period. Due to the lack of empirical evidence on the recruitment rate and adherence to the program by retired physiotherapists, a feasibility study was first conducted.

This upcoming feasibility study would like to modify the existing study design as follows: 1. The G-SS should be scheduled in the timetable when the workload is below 40 h per week. 2. Different retired physiotherapists should be assigned as tutors to each group. The tutors support the students with their longstanding expertise and prepare the students for patient examination and their clinical work under complex conditions. This is intended to create a first link between knowledge acquired so far and its application in practice. 3. Six G-SS cycles should be carried out in the first semester (September 2019 to January 2020) to prepare students for clinical work.

### Aim

The primary aim of this feasibility study will be to evaluate the feasibility of the implementation of G-SS using retired physiotherapists as tutors in an undergraduate physiotherapy educational curriculum in terms of time of task, students’ responsiveness and students’ acceptability of G-SS. Secondary aim will be to investigate the impact of six G-SS cycles on changes in knowledge and skills in pre-clinical physiotherapy students at the BFH-SHP in terms of exam scores. The research question for this study is “What is the impact of retired physiotherapists tutored G-SS versus F-SS in terms of time of task, students’ responsiveness and students’ acceptability of G-SS as well as learning outcome on undergraduate physiotherapy students of BFH-SHP participating in the module basics of physiotherapeutic patient examination?”

## Methods

### Study setting

This study is a part of a study project entitled “Retired PhysioTherapists’Tutor Supported Learning” (RePTusule). The aim of the RePTusule project is to evaluate the effects of G-SS by retired physiotherapists on learning outcomes (practical knowledge) as well as the age images of the physiotherapy students and on the physical performance and cognitive capacity of the retired tutors. This study project will start with this feasibility study. The main study will be conducted after finalization of this feasibility study, which was designed as a prospective, single-center, two-armed, randomized-group controlled educational feasibility study, conducted at the BFH-SHP (Figure 1). A feasibility study will be used prior to the main study to depict important parameters required to design the main study (15). This study will enrol undergraduate first semester physiotherapy students from the BFH-SHP and retired physiotherapists in the role of G-SS tutors.

**Figure 1 fig1:**
[figure not shown]
Flow of the study design.

This study protocol on G-SS is based on the SPIRIT statement (16). The overall project has been approved by the cantonal ethics commission of Bern (2018–01683) and registered in the German Register of Clinical Studies (DKRS: DRKS00015518). The participation will be voluntary. Physiotherapy students can withdraw from this feasibility study at any time. Those who withdraw voluntary from the study will follow the normal curriculum. Their data will not be used for the analysis. Students will be informed both oral and written about the study design and they will sign a consent form agreeing to participate in the study.

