### Intervention program

A total of six G-SS cycles with six different cases will be conducted in the first semester. The intervention program aimed to investigate feasibility and impact of six G-SS sessions on changes in knowledge and skills in pre-clinical physiotherapy students at the BFH-SHP. Students of the G-SS will be divided into five groups of five to six students each. They will work on a clinical case in an 8-day cycle. The structure of the eight-day cycle will be based on Rogan et al. (3, 6, 13, 14, 18). Phase 1, day 1: students of the G-SS and the retired physiotherapists will receive on day 1 (i.e., 1 week prior to the presentation day) via email a clinical case for processing. Phase 2, day 2–7: students will be guided by their tutors during the one-week preparatory phase. Students will have the possibility to arrange two online meeting sessions with their tutor. In these meetings, questions can be answered, and the current status and stumbling blocks can be addressed and solved. Phase 3–5, day 8: students will present their findings and solutions of their work orally and practically. In a moderated plenum session students will conclude the working process and learning process, any questions and optimization steps are clarified. Feedback will be given to the students by the tutors.

The first semester includes topics and learning objectives from the module “Basics of physiotherapeutic Patient Examination.” The topics of the first semester are: basic movement, testing coordination, manual muscle strength tests, massage techniques, movements and joint position, muscle activities, palpation, passive and active angular joint examination, statics and constitution, translational joint examination and tests for muscle flexibility. The G-SS will be scheduled in the school timetable with a total workload of <40 h per week. The case topics are listed in Table 1.

**Table 1 tab1:** Topic of the cases during the G-SS cycles in the first semester.

G-SS cycle	Topic
1.	Massage technique
2.	Joint measurement, differentiation of musculature
3.	Gait analysis
4.	Joint measurement with goniometer and app for comparison
5.	Hip joint region: Examine neighboring joints
6.	Case study in context of Clinical Reasoning

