#### Measures

##### The fidelity of implementation will be assessed for

time of task as (i) participation at all six presentation days (i.e., days 8 of the cycles; phase 3–5), and (ii) the duration of the session on day 8 is limited to maximum 90 min.students’ responsiveness will be recorded by the retired physiotherapists in an attendance list on the presentation day eight. Criteria of success will be defined as at least 83% of the physiotherapy students of the G-SS taking part in five out of six presentation days (i.e., day 8 of the cycles; phase 3–5).

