### Outcome measures

Students’ learning outcome

Students’ learning outcome could be defined as of what a learner is expected to know, understand or be able to do at the end of a period of learning (21). Learning outcome will be measured based on the semester exams (ordinal scaled) including written multiple-choice questions (MCQs) and an Objective Structured Clinical Examination (OSCE). The written exams consist of 87 single best answer MCQs. The OSCE consist of eight 8-min stations. The maximum score will be 87 and 64 points for the MCQs and OSCE, respectively. The exam will be passed if 60% of the total score is reached.Student’s satisfaction will be assessed with the student learning satisfaction questionnaire (22).Self-efficacy will be assessed using the self-efficacy learning (SEL) questionnaire (23).
Level of retired physiotherapists’ physical and cognitive performance. Physical performance capacity will be evaluated using the Short-Physical-Performance-Battery-Test while evaluation of the cognitive performance will be assessed using the Trail-Making A and B test before the start of the tutorship after the end of the first and second semester, respectively.Level of age images of physiotherapy students are assessed before the G-SS and F-SS lessons at the end of first and second semester, respectively. Age images will be assessed with the age images questionnaire (24).Level of G-SS curriculum implementation: the integration of G-SS into the existing curriculum will take place after evaluation of this planned feasibility study (i.e., after the second semester).

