### Data collection methods

The first collection of data by means of surveys is scheduled for the start of the project (T0). Thereafter, the same surveys will be filled out by the students participating in this planned feasibility study after the fall semester (T1) and after the spring semester (T2). Before-and-after learning effects will be shown in the intervention group and the control group as well as between the groups are presenting using parametric methods. If a retired physical therapist, or a physiotherapy student, does not wish to continue participating in this study, that person will, upon request immediately removed from the study program. The date of discontinuation will be noted and placed in the files or records. The data will be anonymized after the analysis.

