### Statistics

Because this study is a feasibility study, testing intervention effects is not a key part of this study design (18). Baseline descriptive statistics will be used to describe G-SS and F-SS group characteristics and to illustrate the feasibility goals. The independent variable will be G-SS. The dependent variable will be the final grades of the MCQs and OSCE. Preliminary group differences at the end of the first semester will be analyzed with the Mann–Whitney-U-Test. The significance level will be set *a priori* to *p* = 0.05. An intention-to-treat analysis will always be the primary analysis of a randomized trial in higher education (17). An ITT will be carried out if physiotherapy students do not adhere to the G-SS protocol.

The findings of the satisfaction and self-efficacy items will be summarized visually in a table and presented as response distributions (number, percentage). Satisfaction analysis will involve the summation satisfaction scale scores, with 0.80 as the proposed threshold for defining usability and acceptability, counting only positive endorsements (4 = agree, 5 = strongly agree). Qualitative data from the semi-structured interview will be analyzed thematically.

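### Excluding all data of students who withdraw conflicts with intention-to-treat as the primary analysis and, if applied to the 83% responsiveness criterion, can turn a missed target into a met one

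*Protocol article*

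**What the plan says.** Four places in the protocol article bear on this point.

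- **Methods, Study setting (paragraph after Figure 1).** Leaving is unrestricted: "Physiotherapy students can withdraw from this feasibility study at any time". The consequence follows: "Those who withdraw voluntary from the study will follow the normal curriculum. Their data will not be used for the analysis".
- **Statistics.** The principle is general: "An intention-to-treat analysis will always be the primary analysis of a randomized trial in higher education (17"). The next sentence makes it depend on an event: "An ITT will be carried out if physiotherapy students do not adhere to the G-SS protocol".
- **Measures, fidelity of implementation.** Success on responsiveness is "at least 83% of the physiotherapy students of the G-SS taking part in five out of six presentation days". The section does not say whether withdrawn students still count as G-SS students.
- **Data collection methods.** For anyone who stops, "The date of discontinuation will be noted and placed in the files or records". Nothing is said there about deleting or setting aside data.

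No section separates stopping participation from revoking consent to the use of data.

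**The concern.** A student who leaves G-SS part-way and returns to ordinary teaching is the plainest case of non-adherence, which is what the Statistics section means intention-to-treat to cover. The Study setting section removes that same student. An analyst cannot tell from the article which rule governs.

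The choice affects a primary feasibility measure. The Abstract describes the 83% threshold in terms of willingness to take part, and withdrawal is a direct sign of unwillingness. If withdrawn students are not counted, the measure leaves out some of the people it is meant to detect. The Study setting section says that this study is to supply parameters for designing the main study, and an overstated responsiveness figure would carry over into that design.

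For the exam comparison, exclusion after assignment means that the two sets of students compared are no longer those formed by randomisation.

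**Working it through.** **1. The two rules side by side.** Intention-to-treat analyses students in the arm to which their group was assigned, whatever they later did. The Study setting rule analyses only those who did not withdraw. The two agree only if nobody withdraws. The conditional sentence in Statistics does not bridge the gap: it limits intention-to-treat to non-adherence, whereas the sentence before it says the analysis is always primary.

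**2. Inputs for the responsiveness criterion.**

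- Threshold: 83% (Measures).
- Arm size: "Students of the G-SS will be divided into five groups of five to six students each" (Intervention program), so N = 5 × 5 = 25 to 5 × 6 = 30.
- Number withdrawing, w: not given, so assumed below.
- The article gives no calculation on this point to reproduce.

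**3. Formula.** Let s be the number attending at least five of the six presentation days. With all assigned students counted, the proportion is s/N. If w students who had not reached five days withdraw and are removed, it becomes s/(N − w), which is larger whenever w > 0 and s > 0.

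**4. Attenders needed with everyone counted.** N = 25: 0.83 × 25 = 20.75, so 21. N = 30: 0.83 × 30 = 24.9, so 25.

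**5. Results under assumed withdrawals.**

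| N | w | s | All assigned | Withdrawn removed |
|---|---|---|---|---|
| 25 | 1 | 20 | 20/25 = 80.0%, not met | 20/24 = 83.3%, met |
| 30 | 2 | 24 | 24/30 = 80.0%, not met | 24/28 = 85.7%, met |
| 30 | 5 | 21 | 21/30 = 70.0%, not met | 21/25 = 84.0%, met |
| 30 | 6 | 20 | 20/30 = 66.7%, not met | 20/24 = 83.3%, met |

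With N = 30 a single withdrawal does not lower the requirement: 0.83 × 29 = 24.07, so 25 attenders are still needed.

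**6. The opposite case.** If the student removed had already attended five days, both numerator and denominator fall. With N = 30 and s = 25, 25/30 = 83.3% (met) becomes 24/29 = 82.8% (not met).

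**7. Chance of meeting 83%, by simulation.** Attendance of each student is binomial, and a fixed share of the non-attenders withdraws. The attendance rates and shares are assumptions.

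| True share attending | Share of non-attenders withdrawing | N = 25: all assigned → withdrawn removed | N = 30: all assigned → withdrawn removed |
|---|---|---|---|
| 75% | one quarter | 0.21 → 0.39 | 0.20 → 0.34 |
| 75% | one half | 0.22 → 0.65 | 0.20 → 0.67 |
| 70% | one quarter | 0.09 → 0.21 | 0.08 → 0.17 |
| 70% | one half | 0.09 → 0.49 | 0.08 → 0.49 |

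**8. Exam comparison.** "Learning outcome will be measured based on the semester exams (ordinal scaled) including written multiple-choice questions (MCQs") and an OSCE, compared by the Mann–Whitney test at 0.05 (taken as two-sided). Assume no true effect, normal scores, independent students and withdrawal in G-SS only. If the weakest fraction q leaves, the G-SS mean shifts by φ(z_q)/(1 − q), which is 0.195 SD for q = 10% and 0.350 SD for q = 20%. In simulation with 30 per arm, rejection goes from about 5% to about 11% and 24%. With a correlation of 0.5 between ability and staying, the shifts are about 0.09 and 0.17 SD and rejection about 6% and 9%. With unrelated withdrawal there is no shift. With a correlation of −0.5 the shifts are about −0.09 and −0.17 SD, so the size is similar and the sign reversed.

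**The case against.** The strongest defence is that the two rules address different students. The exclusion sentence stands in a paragraph on voluntariness and consent and concerns leaving the study. The intention-to-treat sentence concerns students who do not follow G-SS, and a student can miss sessions without leaving. On that reading non-adherers who stay are analysed as assigned, and only leavers are set aside. The rule may also reflect a consent or ethics condition that the article does not show. This reading is workable, but it is not intention-to-treat and does not fit a statement that intention-to-treat is always primary. The boundary would still have to be written down.

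Some further points stand, and they limit what may be concluded:

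- The article does not say that withdrawn students leave the 83% denominator. That follows only if the exclusion is applied there. Because discontinuation dates are recorded, drop-out can still be reported.
- A reader might infer that the primary feasibility result as a whole is biased towards success. The documents do not support that. Responsiveness is one of several criteria, and tutor recruitment, for example, is unaffected by student withdrawal. The rise also occurs only when those who leave had not attended five days.
- A reader might infer that drop-out will be higher in G-SS because it demands extra work. The article gives controls the same timetabled time and schedules G-SS in weeks below 40 hours, so differential drop-out is possible but is an assumption.
- A reader might infer that the exam comparison will favour G-SS. The direction depends on who leaves, and the Statistics section says that testing effects is not a key part of the design.
- Acceptability has no denominator to correct. It is assessed with open questions after the sixth cycle, and the qualitative data are analysed thematically. The 0.80 threshold in Statistics belongs to the satisfaction scale.

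**Conclusion.** The conflict between the exclusion rule and the intention-to-treat statement is in the text and needs resolving. Its main practical effect is on the 83% responsiveness criterion. If the exclusion is applied there, one withdrawal among 25 students or two among 30 can reverse the result from 80% (not met) to 83.3% or 85.7% (met). This rests on assumed withdrawal numbers and on the leavers not having attended five days. The arithmetic direction is certain only under that second condition.

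The exam comparison loses the protection of randomisation, with possible bias in either direction or none. This matters less, because the outcome is secondary and preliminary. The documents do not support a claim that the whole feasibility assessment, or the exam result, will be inflated.

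**What to change.** Replace the exclusion sentence in Methods, Study setting with wording such as:

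> All consenting students are analysed in the arm to which their group was assigned. Students who withdraw stay in the denominator of the 83% responsiveness criterion, with missed sessions counted as not attended. Data collected before withdrawal and semester exam scores are used unless the student also revokes consent to data use.

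In Statistics, make the intention-to-treat sentence unconditional and keep any completers' analysis as a sensitivity analysis. Report the number of withdrawals by arm, and show it alongside the acceptability results so that readers can see whose views are missing.

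The cost is small. Attendance is already listed by the tutors on each presentation day. Students who withdraw go back to ordinary teaching, so their semester exam scores should normally exist (an inference; the article does not say so). The consent wording must separate stopping participation from revoking data use, and the responsiveness figure may come out less favourable.
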